## Abstract

**Background:**

Cleft lip and palate is a complex congenital defect that can present functional and esthetic challenges, particularly in patients with large alveolar clefts for which surgical management is indicated. In contrast to traditional treatment techniques such as autologous bone grafting, newer techniques include unilateral Le Fort I osteotomy advancement and dentoalveolar transport distraction osteogenesis and have been shown to be useful in the treatment of maxillary hypoplasia and large alveolar clefts. These techniques may help improve both esthetic and function in patients with substantial tissue deficiencies as well as in patients with scarring.

**Objective:**

This study aims to compare the outcomes of unilateral Le Fort I advancement and dentoalveolar transport distraction in the management of large alveolar clefts, specifically focusing on the closure of alveolar gaps, maxillary arch form, stability of the advanced or distracted segment, and wound healing.

**Methods:**

This prospective observational study is being conducted at the Department of Oral and Maxillofacial Surgery, Siddharth Gupta Memorial Cancer Hospital, in collaboration with the Sharad Pawar Dental College in Maharashtra, India. Patients aged 9 to 25 years with unilateral alveolar clefts measuring 1 cm or greater will be included. Patients with smaller clefts, bilateral clefts, or those who are unsuitable for surgery will be excluded. The study will evaluate 14 patients, divided into 2 groups: group A will undergo dentoalveolar transport distraction, whereas group B will undergo unilateral Le Fort I advancement. We will assess the closure of the alveolar gap, arch form, stability of the advanced or distracted segment, and soft tissue healing. Through cone beam computed tomography and maxillary occlusal view, radiographic parameters of closure of the alveolar gap and arch form will be evaluated. The outcome measures will be statistically analyzed on RStudio software, with appropriate tests applied to each outcome measure. *P*<.05 will be considered significant.

**Results:**

As of June 2025, institutional ethical clearance has been obtained and patient recruitment is ongoing. Recruitment began in April 2023, with 12 patients enrolled as of June 2025. Data collection is expected to be completed by December 2025, and results will be published in mid-2026.

**Conclusions:**

This study aims to provide evidence-based guidance for the management of large alveolar clefts by comparing 2 graftless surgical techniques: unilateral Le Fort I advancement and dentoalveolar transport distraction. The findings are expected to help clinicians select the most suitable surgical approach based on individual case requirements, cleft morphology, and long-term outcome expectations. Ultimately, the study will contribute to optimizing cleft care strategies with reduced donor site morbidity and improved postoperative stability.

## Introduction

Cleft lip and cleft palate are among the most common congenital craniofacial anomalies, occurring in approximately 1 in every 700 live births globally, with variability based on ethnicity, gender, and geography [1]. These anomalies arise from the failure of normal fusion of facial processes during early intrauterine life and can occur in isolation or combination, unilaterally or bilaterally [2]. Alveolar clefts, often accompanying cleft lip or palate, result from a failure in primary palate formation, leading to discontinuity in the maxillary arch. This disrupts dental development, speech, mastication, and nasal function and predisposes individuals to oronasal fistulae [3].

The traditional method for alveolar cleft management has been secondary alveolar bone grafting (SABG), introduced by Boyne and Sands in 1976 [4]. SABG aims to bridge the cleft with autogenous cancellous bone, typically from the iliac crest, to allow tooth eruption and stabilize the arch. Despite its widespread use, SABG presents limitations, especially in large clefts, due to issues such as donor site morbidity, unpredictable graft resorption, and soft tissue insufficiency leading to wound dehiscence [5,6]. These drawbacks have led to the exploration of graftless alternatives such as distraction osteogenesis (DO).

DO, first applied to the craniofacial skeleton by McCarthy et al (1992) [7], involves gradual movement of bone segments to promote new bone formation. Dentoalveolar transport distraction, a subset of DO, has demonstrated effectiveness in reducing cleft width and promoting both bone and soft tissue regeneration, particularly in wide alveolar defects where bone grafting may fail [8-10]. Unilateral Le Fort I advancement, another surgical technique, enables forward repositioning of the cleft-side maxilla to close the defect while simultaneously correcting midface retrusion [11]. Both techniques offer graftless solutions with promising outcomes, although comparative clinical data between them remain limited.

Considering the complexity of large alveolar clefts and the limitations of conventional bone grafting, this study aims to evaluate the outcomes of dentoalveolar transport distraction compared with unilateral Le Fort I advancement. The analysis will focus on cleft gap closure, maxillary arch form, the stability of mobilized section, and postoperative healing. This comparative assessment will offer sought-after information to direct surgical decision-making in the treatment of wide alveolar clefts, as the traditional techniques often fail due to graft resorption, soft tissue dehiscence, or inadequate bone regeneration.

While both unilateral Le Fort I advancement and dentoalveolar transport distraction have been independently used for managing large alveolar clefts, comparative clinical data between these 2 techniques are lacking. Current literature focuses on individual case series or retrospective studies, with no consensus on which method yields superior outcomes in terms of bone regeneration, stability, or soft tissue healing. Given the unpredictability and donor site morbidity of traditional grafting methods in wide clefts, a direct prospective comparison of these 2 graftless techniques is warranted. This study aims to fill that gap by systematically evaluating and comparing the clinical, esthetic, and radiographic outcomes of both procedures in patients with large alveolar clefts.

To guide the comparison between unilateral Le Fort I advancement and dentoalveolar transport distraction in the management of large alveolar clefts, the following hypotheses were formulated:

Alternate hypothesis—there is a detectable difference between unilateral Le Fort I advancement and dentoalveolar transport distraction in at least 1 of the following outcomes: alveolar gap closure (measured radiographically), arch form (classified clinically and radiographically), stability of the mobilized segment (graded on the bone stability scale), or soft tissue healing (graded on the Landry wound healing scale) in patients with large alveolar clefts.Null hypothesis—there is no detectable difference between unilateral Le Fort I advancement and dentoalveolar transport distraction in alveolar gap closure, arch form, segment stability, or soft tissue healing outcomes in patients with large alveolar clefts.

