### Primary Objective

The primary objective will be to compare the outcomes of unilateral Le Fort I advancement and dentoalveolar transport distraction in the closure of alveolar gap, arch form, segment stability, and soft tissue healing.

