### Sample Size Calculation

The minimum required sample size was calculated using the standard formula for comparing 2 independent means, as shown below:

$$N=\frac{{\left(Z_{\alpha }+Z_{\beta }\right)}^{2}\left(P_{1}\left(1-P_{1}\right)+P_{2}\left(1-P_{2}\right)\;\right)}{{\left(P2-P1\right)}^{2}}$$

$$Z_{\alpha }=1.64$$

α= Type I error at 5%

$$Z_{\beta }=0.84$$

β= Type II error at 20%

The following parameters were used for the sample size calculation:

Improved facial esthetic and balance in maxillary DO=94%Improved facial esthetic and balance in maxillary unilateral Le Fort 1 osteotomy=44% (estimated clinically significant difference=50%)Difference (P2−P1)=50%Minimum sample size N=2×(1.64+0.84)^2^ (0.94) (1‐0.94) + 0.44(1‐0.44)/(0.50)^2^=7 each in 2 groupsSample size=14, with 7 in each group

Using a 2-sided z test with *α*=.05 and power of 80%, assuming a success rate of 94% in the dentoalveolar transport distraction group and 44% in the unilateral Le Fort I advancement group, the required sample size is 7 per group (N=14). This includes a 50% absolute effect size and accounts for variability in response.

The 50% effect size estimate was based on the internal pilot data and clinical observations. However, we acknowledge the possibility of overestimation. A sensitivity analysis will also consider a 40% effect size, which would require a larger sample and will be addressed in future studies.

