### Primary Outcome

The primary outcomes evaluated in this study will be as follows:

Closure of the alveolar gap: measured clinically and radiographically (ie, CBCT) at 5 time points: preoperatively; immediately after surgery; and at 1, 3, and 6 months and 1 year of follow-upArch form: classified (U-shaped, V-shaped, or asymmetrical) via models and radiographs at each follow-up

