### Secondary Outcomes

The secondary outcomes assessed in this study will include the following:

Stability of the advanced or transported segment: evaluated by bidigital palpation and CBCT and graded on a 5-point bone stability scale (1=highly unstable; 5=highly stable).Soft tissue healing: evaluated by the Landry wound healing scale at all times of follow-up and graded from 1 (very poor) to 5 (excellent).

All outcome assessments will be performed by evaluators who are blinded to the treatment group. CBCT scans will be anonymized, coded, and randomized before analysis. In cases where unblinding may occur (eg, visible hardware on radiographs), a second independent blinded reviewer will reassess.

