### Statistical Analysis

All data will be analyzed using RStudio (version 4.3.2; Posit, PBC). Continuous variables (eg, cleft width and bone segment stability score) will be tested for normality using the Shapiro-Wilk test. Depending on data distribution, between-group comparisons will be performed using either the unpaired *t* test (for normally distributed data) or the Mann-Whitney *U* test (for nonparametric data). Categorical outcomes, such as arch form classification (U-shaped, V-shaped, or asymmetrical) and wound healing grades (from the Landry wound healing scale), will be compared using the chi-square test or Fisher exact test, as appropriate.

Longitudinal outcomes (eg, segment stability across time points) will be analyzed using repeated measures ANOVA for normally distributed data or generalized estimating equations for nonparametric repeated measures. All outcome measures will be reported with 95% CIs, and *P*<.05 will be considered statistically significant. Missing data will be handled using multiple imputation, and any potential confounders, such as age or initial cleft width, will be adjusted for using multivariate regression analysis.

To assess the robustness of results, sensitivity analysis will be conducted by comparing results from multiple imputation with complete-case analysis and worst-case scenario imputation.

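### A difference on any one of four outcomes at an unadjusted P<.05 satisfies the study hypothesis, so the false-positive rate is about 13% to 18.5% rather than 5%, and the protocol does not settle which outcomes are primary

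*Protocol article*

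**What the plan says.** All places are in the protocol article.

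- **Introduction (hypotheses).** The alternative is a union: "there is a detectable difference between unilateral Le Fort I advancement and dentoalveolar transport distraction in at least 1 of the following outcomes". Gap closure, arch form, segment stability and soft tissue healing follow. The null is no difference on any of them.
- **Primary Objective.** The two techniques are to be compared "in the closure of alveolar gap, arch form, segment stability, and soft tissue healing", which is all four outcomes.
- **Primary Outcome.** "The primary outcomes evaluated in this study will be as follows" is followed by two items only, gap closure and arch form. The schedule for gap closure is announced as five time points, but six are listed: one preoperative and five postoperative. No visit is singled out.
- **Secondary Outcomes.** This section holds the other two: "Stability of the advanced or transported segment: evaluated by bidigital palpation and CBCT", and soft tissue healing on the Landry scale.
- **Statistical Analysis.** Two-group tests are named by type of variable, and repeated measures ANOVA or generalized estimating equations (GEE) for longitudinal outcomes. "All outcome measures will be reported with 95% CIs", and P<.05 "will be considered statistically significant". No correction or order of testing is given. The Abstract repeats the threshold, with a suitable test for each outcome.
- **Postoperative Care.** Unadjusted and regression-adjusted results are to be reported side by side, and a propensity score adjustment is added.

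**The concern.** When a hypothesis is met by any one of several outcomes, the error rate that matters is the chance that at least one test is significant when none of the outcomes differs. Testing each at 5% does not hold that chance at 5%.

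Two further gaps leave room for choice after the data are seen. The protocol gives two versions of what is primary, and it fixes no visit. The Abstract and Discussion say the findings are meant to guide the choice of technique and may feed into treatment guidelines. With 14 patients, a chance result on one of four scales could be reported as support for the study hypothesis.

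**Working it through.** **Inputs from the protocol.** Four outcomes under an at-least-one rule (Introduction); two listed primaries (Primary Outcome); P<.05 per test (Statistical Analysis); 7 per group and a two-sided 5% level (Sample Size Calculation); five postoperative assessments (Outcome Measures and Data Collection).

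**Assumed, because the protocol does not give them.** Correlation between outcomes 0 to 0.5, correlation between visits 0 to 0.9, and the category frequencies of the ordinal and nominal scales.

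**1. The plan's own level.** One outcome tested once gives 1 − 0.95 = 5%. The stated level is right for a single test only.

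**2. One test per outcome, independent tests.** The rate is 1 − 0.95^k.
- Two listed primaries: 1 − 0.95² = 9.8%.
- Four outcomes: 1 − 0.95⁴ = 18.5%.

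With normal test statistics correlated at 0.3 to 0.5, the four-outcome figure falls only to about 17% to 16%.

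**3. One test per outcome, small-sample tests.** Null data were simulated with 7 per group, 3,000 runs per scenario. The tests were a t test for gap, exact Fisher-type tests for arch form and Landry grade, and Mann-Whitney for stability. Discrete tests reject less often than 5%: with all correlations zero, the single-test rates were 4.5% (gap), 2.5% (arch form), 3.2% (stability) and 3.2% (healing). These give 1 − 0.955 × 0.975 × 0.968 × 0.968 ≈ 12.8%, which matches the simulated rate.

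| Correlation: outcomes / visits | 2 primaries, one visit | 4 outcomes, one visit | 2 × 5 visits | 4 × 5 visits |
|---|---|---|---|---|
| 0 / 0 | 6.9% | 12.8% | 32.8% | 52.8% |
| 0 / 0.5 | 7.1% | 14.5% | 29.1% | 50.9% |
| 0.3 / 0.5 | 8.3% | 15.3% | 29.5% | 48.3% |
| 0.3 / 0.7 | 7.8% | 15.0% | 25.8% | 44.3% |
| 0.5 / 0.8 | 8.0% | 13.6% | 21.3% | 37.5% |
| 0.5 / 0.9 | 6.9% | 13.0% | 19.9% | 34.5% |

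The Monte Carlo standard error is about 0.6 percentage points near 14% (√(0.14 × 0.86 / 3000)), so the one-visit rows hardly differ from each other. The last two columns apply only if every visit were tested separately. The independence figure for 20 tests is 1 − 0.95²⁰ = 64.2%.

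**4. Keeping the four-outcome rule with control.** Bonferroni gives 0.05/4 = 0.0125 per outcome. The plan's 7 per group comes from (1.64 + 0.84)² × (0.94 × 0.06 + 0.44 × 0.56) / 0.50² = 7.45, for a facial esthetics endpoint ("Improved facial esthetic and balance in maxillary DO=94" percent against 44%). At those rates and two-sided 0.0125, the unpooled formula gives 13.5, so 14 per group (18 with pooled variance). Power with 7 per group is about 29% by normal approximation, against about 53% at two-sided 0.05.

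**5. Which visit is reachable.** Results reports 12 of 14 enrolled in June 2025, recruitment still open, and data collection ending in December 2025. Anyone enrolled after December 2024 has less than 12 months. Anyone enrolled after June 2025 has less than 6 months, and surgery follows enrolment.

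**The case against.** **Visits.** A reader might infer that a difference is claimed if any outcome is significant at any visit, and quote 64%. The documents do not support that. The hypothesis does not mention visits, no section says each visit is tested and claimed separately, and Statistical Analysis names repeated measures ANOVA or GEE, which could give one or two group comparisons per outcome. Five visits is also the upper count: Postoperative Care schedules four follow-up visits. At the immediate postoperative assessment, gap width is no fair null comparison, since distraction starts only after the latency period while the Le Fort segment is moved at surgery. This objection stands, so the by-visit figures are a worst case. They are not fanciful, however: the only comparison explicitly named for arch form and Landry grade is chi-square or Fisher, and no visit is attached to it.

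**Conflict over what is primary.** A reader might infer that this conflict itself raises the error rate. It does not. It leaves open whether two or four outcomes must be controlled.

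**Which estimate decides.** Postoperative Care says regression will adjust the primary effect estimates, which leans towards the adjusted result. That is fair, but the role of the propensity score stays open.

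**A separate analysis plan.** One may exist and may add control. It would still have to override the hypothesis or the objective as published, and these sections would still disagree.

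**Proportion.** In a nonrandomized study with allocation by the surgeon, confounding may matter more than nominal alpha. That may be so, but it does not make the stated 5% correct.

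**Conclusion.** The point holds at the level of outcomes. As written, the study hypothesis has a false-positive rate of about 13% to 15% (simulated at 7 per group, assumed correlations and category frequencies) up to 18.5% (independent tests at their nominal level), with only one test per outcome. That is roughly 2.5 to 4 times the stated 5%. If the two listed primaries are the family, the excess is modest: about 7% to 8% simulated, 9.8% nominal.

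Primary Objective and the two outcome sections contradict each other on what is primary, and no primary time point is named. Both leave the test family open.

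Separate testing at all five postoperative visits would give about 35% to 53% under the assumed correlations, or 64% if independent. That is a worst case under an assumption, not a rule that the protocol states.

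**What to change.** Before analysis, by dated amendment that records who has seen outcome data:

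1. Align the hypotheses in the Introduction and the Primary Objective with the Primary Outcome section, and correct the count of time points there.
2. Name one primary comparison at two-sided 5%, for example CBCT gap width at one stated visit, adjusted for baseline gap. Alternatively, keep gap closure and arch form as two primaries at that visit with Holm: the smaller P against 0.025 and, if that is met, the other against 0.05.
3. Choose a visit that every patient can reach by December 2025, or move the closing date.
4. State which estimate decides: unadjusted, regression-adjusted or propensity-adjusted.
5. Report stability, soft tissue healing and all other visits as secondary, with estimates and confidence intervals and no confirmatory claims.

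No new measurements are needed, and regression of gap width with baseline cleft width is already planned. The cost is that fewer results may be called significant, and follow-up runs longer if 12 months is chosen. The Sample Size Calculation rests on facial esthetics, so it does not support the named primary; the amendment should say so. Choosing a primary with 12 of 14 patients enrolled is late, which is why the date and the statement on data access matter.

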## Methods

### Overview

This is a nonrandomized, prospective observational study conducted at the Department of Oral and Maxillofacial Surgery, Siddharth Gupta Memorial Cancer Hospital, in collaboration with Sharad Pawar Dental College, Maharashtra, India. The estimated study duration is from April 2023 to December 2025.

A total of 17 patients have been screened, of whom 70.58% (12/17) participants have met the eligibility criteria and have been enrolled. Patients have been allocated to 1 of 2 intervention groups (dentoalveolar transport distraction or unilateral Le Fort I advancement) based on individualized clinical considerations, including cleft morphology, available bone stock, and expected compliance with the treatment protocol. Allocation was determined by the treating maxillofacial surgeon in accordance with predefined feasibility criteria.

### Ethical Considerations

This study was reviewed and approved by the Institutional Ethics Committee of Datta Meghe Institute of Higher Education and Research (DMIHER(DU)/IEC/2023/843). All procedures performed will be in accordance with the ethical standards of the responsible institutional committee and with the principles of the Declaration of Helsinki. Written informed consent has been obtained from all participants (or their legal guardians when applicable) prior to inclusion in the study. Participant data will be anonymized, and confidentiality and privacy of all individuals will be maintained according to institutional and national regulations. No personal identifying information will be disclosed. No compensation will be provided to participants for their involvement in the study.

### Intervention Delivery

All surgeries will be performed by experienced oral and maxillofacial surgeons under general anesthesia.

The surgical procedures for both study groups will be standardized and carried out according to established protocols, as outlined below:

In *group A (dentoalveolar transport distraction)*, after adequate orthodontic preparation and osteotomy, a custom-fabricated intraoral distractor was placed. Distraction commenced after a latency period of 5 to 7 days, at a rate of 1 mm per day until gap closure, followed by a consolidation period of 8 to 12 weeks.In *group B (unilateral Le Fort I advancement)*, standard Le Fort I and palatal osteotomies were performed. The cleft-side maxillary segment was repositioned medially and stabilized using a surgical splint and titanium plates.

Postoperative care will be standardized across both groups and included antibiotics, analgesics, antiseptic rinses, and dietary modifications.

### Outcome Measures and Data Collection

Data collection will occur at predefined intervals: preoperatively; immediately after surgery; and at 1, 3, 6, and 12 months of follow-up.

The following outcome variables will be systematically evaluated in both groups:

Alveolar gap closure will be measured radiographically using cone beam computed tomography (CBCT) at each interval.Maxillary arch form will be classified (U-shaped, V-shaped, or asymmetrical) using dental models and occlusal views.Segment stability will be assessed clinically and via CBCT using the 5-point bone stability scale.Soft tissue healing will be evaluated by blinded assessors using the Landry wound healing scale.

All CBCT images will be anonymized and randomized. Two independent evaluators, blinded to group assignment, will perform measurements. If visible hardware reveals the treatment allocation, a second reviewer re-evaluated the image independently.

